**Methods::**

This study is a multicenter, double-blind, randomized, placebo controlled clinical trial in which 60 eligible participants were randomly divided into an experimental group and control group at a 1:2 ratio. Both groups received the same basic treatment for DF disease, the experimental group used FBD and ordinary dressing changes, while half of the patients in the control group received placebo and ordinary dressings, and the other half received placebo and silver ion dressings. Patients in both groups will be evaluated weekly for efficacy during the intervention. The primary efficacy indicators include the types of wound pathogens, interleukin 6 and tumor necrosis factor α. Secondary efficacy indicators included blood glucose, blood lipids, wound area, lower extremity blood vessel diameter, blood flow speed, walking speed, walking distance, and traditional Chinese medicine syndrome scores. We will also conduct a safety evaluation of the drug at the end of the trial.

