Recently meta-analysis has shown that TCM foot bath can significantly improve the sensory nerve conduction velocity, motor nerve conduction velocity, and neuropathy syndrome scores in patients with diabetic peripheral neuropathy, and has certain advantages in alleviating its clinical symptoms.^[23]^ Foot bath can inhibit bacteria through the environmental changes on the surface of foot ulcers. Several studies have shown that the anti-inflammatory effect of herbal medicine foot bath may be achieved by lowering blood glucose and reducing the number of hypersensitive C-reactive protein and white blood cells.^[24]^ Based on the above conclusions, we hypothesized that FBD can both regulate and inhibit local bacteria to promote healing of DF wounds.

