### Sample size

2.4

This study is a superiority clinical trial with interleukin 6 (IL-6) as the main efficacy indicator, so we chose the mean superiority test of 2 independent samples to estimate the sample size. According to the previous relevant references,^[25]^ the optimal response rate was set to 0.04. The mean values of the experimental group and the control group were 6.14 and 6.21, and the combined standard deviation of the 2 groups was 0.14. At the same time, set *a* to 0.025 and *b* to 0.2. Enter the above values into the Power Analysis and Sample Size version 11.0 (PASS 11.0) software to calculate the sample size for the experimental group as 20 and the control group as 40. Finally, the total number of study samples is determined to be 60 cases.

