### Outcome measures

3.2

Primary efficacy outcomes:

1.IL-6 and tumor necrosis factor α (TNF-α) were detected by enzyme-linked immunosorbent assay and were measured before and each week after treatment during entire treatment.2.Wound pathogen distribution: Collect samples of ulcers and use a fully automatic microbiologic tester for bacterial detection once a week.

Secondary efficacy outcomes:

1.Blood glucose and blood lipid: The blood glucose, total cholesterol, triglyceride, low-density lipoprotein cholesterol, and high-density lipoprotein cholesterol are detected by a fully automatic biochemical analyzer.2.Wound area: Long multiplied by high area. First take a picture of the wound and then read the data with Image J software. The above operations are performed by the same doctor.3.Lower extremity blood vessel diameter, blood flow velocity: detected by lower extremity blood vessel Doppler ultrasound.4.Walking speed, walking distance: Make patients walk on a flat ground with a scale, and calculate the distance and speed.5.TCM syndrome score: Recorded with TCM Syndrome Score Evaluation Form.

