### Statistical analysis

3.5

The data of the study will be analyzed by statistical analysis software packages SPSS 23.0 and will be performed by experts from the Statistics Teaching and Research Office of Chengdu University of Traditional Chinese Medicine. The measurement results was calculated by *t* test, and the results were expressed as “mean ± standard deviation.” Chi-squared test was used to analyze the count data. The paired design *t* test was used for comparison the differences between before and after treatment with the same group, and the independent sample *t* test was used for comparison the differences between groups. The comparison of incidence of adverse events between the 2 groups using Chi-squared test or Fisher exact probability method. If *P* < .05, it was considered as a statistically significant difference.

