## Discussion

4

The DF is a serious public health problem in global health, which not only affects the quality of life of patients and families, but also greatly increases the financial burden on health care. DFI is an important reason for aggravating the long-term nonhealing of DF.^[31]^ The current mainstream treatment of DFI is mainly to choose sensitive antibiotics, but long-term use will make the body less sensitive or accelerate the production of drug-resistant bacteria, so more complementary therapies need to be sought. Herbal medicine foot bath has a long history of treating surgical diseases and shows the unique advantages that are different from WM, namely significant clinical efficacy and few adverse reactions. FBD is a TCM compound that has been used in DF for a long time in our hospital's endocrinology department. Due to lack of evidence on the efficacy and safety of FBD for the treatment of DFI, we need conduct a randomized, double-blind clinical trial to determine the risks and benefits of using a FBD for DFI.

As we all know, this is the 1st clinical study to treat DFI with TCM FBD. Throughout the treatment period, we closely focused on the distribution of bacterial wounds, indicators of inflammation, ulcer healing, limb function, and drug safety. We will verify that FBD can inhibit the bacterial growth of wounds through objective indicators of bacterial culture, IL-6, and TNF-α. At the same time, the overall effect of the foot bath prescription is reflected by the change in the area of the wound, the walking distance and speed, the inner diameter of the lower extremity blood vessels, the blood flow velocity, and the TCM syndrome score table. Finally, the safety evaluation was reflected by blood cell analysis, urine analysis, stool testing, liver and kidney function indicators, and so on.

However, there were plenty of limitations in our trial. On the one hand, due to the small sample size of the subjects, large-scale data are lacking to confirm the efficacy of the foot bath prescription. On the other hand, the mechanism of action of FBD is not complete, and further research is necessary. We need to observe a large sample size in future research to understand its accuracy and rationality.

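### Wound area is defined as length times height although each wound is already photographed and read in ImageJ; a traced outline would be a modest, nearly free improvement to a secondary outcome.

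*Protocol article*

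**What the plan says.** Section 3.2 (Outcome measures) lists wound area as a secondary efficacy outcome and defines it in one item: "Long multiplied by high area. First take a picture of the wound and then read the data with Image J software". The item adds: "The above operations are performed by the same doctor". It mentions no outline tracing, no ellipse correction and no scale in the photograph, and it does not say along which axes the two lengths are taken.

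The abstract gives the same role: "Secondary efficacy indicators included blood glucose, blood lipids, wound area, lower extremity blood vessel diameter, blood flow speed, walking speed, walking distance". The Introduction makes healing part of the hypothesis: "we hypothesized that FBD can both regulate and inhibit local bacteria to promote healing of DF wounds". Section 4 (Discussion) says that "the overall effect of the foot bath prescription is reflected by the change in the area of the wound", together with walking, vascular and syndrome-score measures. Section 3.5 plans the group comparison thus: "the independent sample *t* test was used for comparison the differences between groups".

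**The concern.** A length-by-height product is the area of a rectangle drawn around the ulcer. It exceeds the true area of any wound that does not fill that rectangle, and the excess depends on shape. If shape changes as the wound is debrided, contracts or closes unevenly, the error does not cancel between visits and adds noise to the change in area.

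Among the listed outcomes, wound area is the only one that directly measures wound size; closure, time to healing and amputation are not listed. Avoidable measurement error here weakens the trial's most direct evidence on healing. The means to avoid it, a photograph opened in ImageJ by a single reader, are already in the procedure.

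**Working it through.** The article states no figure for wound area, so there is nothing of the plan's own to reproduce.

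**Inputs from the article.** The product definition and the single ImageJ reader (section 3.2); the independent-samples t test (section 3.5); 20 experimental and 40 control patients (section 2.4, "calculate the sample size for the experimental group as 20 and the control group as 40"). All other inputs below are assumptions.

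**1. Absolute area.** An ellipse with axes L and H has area πLH/4. The ratio of product to true area is 4/π = 1.273, an overstatement of 27.3%. This holds when L and H are the wound's own axes. If the height is instead read along the picture's vertical and the wound lies at 45 degrees, the overstatement is 38%, 59% or 112% for axis ratios of 1.5, 2 or 3.

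**2. A constant factor does no harm to the comparison.** Multiplying every area by 1.273 leaves percent change and the t statistic unchanged. In a simulation of 20 versus 40 patients (two-sided 0.05, area coefficient of variation 0.5, 30% group difference), power was 0.71 on true area and 0.71 on area times 4/π.

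**3. A varying factor does.** Let f = true area / (L × H), the fill factor. Then

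apparent reduction = 1 − (1 − true reduction) × f₀/f₁.

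For a true 40% reduction:
- f constant: 1 − 0.60 = 40%.
- f from 0.785 to 0.65: 1 − 0.60 × 0.785/0.65 = 27.5%.
- f from 0.65 to 0.785: 1 − 0.60 × 0.65/0.785 = 50.3%.

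**4. Effect on power.** Assume that relative area (end/baseline) has SD 0.25, that controls average 0.6, that f has mean 0.75 with SD s and correlation ρ between visits, and that the true difference gives 80% power on error-free area. To first order:
- The coefficient of variation of f₀/f₁ is (s/0.75) × √(2(1 − ρ)).
- The added SD is 0.6 times that.
- Power ≈ Φ(2.80 × 0.25/total SD − 1.96), where 2.80 = 1.96 + 0.84.

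For s = 0.08 and ρ = 0: the coefficient of variation is 0.107 × 1.414 = 0.151; the added SD is 0.6 × 0.151 = 0.090; the total SD is √(0.0625 + 0.0082) = 0.266; power ≈ Φ(2.63 − 1.96) = 75%. Simulation agrees with this approximation:

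| Shape correlation between visits | s = 0.05 | s = 0.08 | s = 0.12 |
|---|---|---|---|
| 0 (independent) | 78% | 74–75% | 67–69% |
| 0.5 | 79% | 78% | 74% |
| 0.8 | 79% | 79% | 78% |

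The loss from 80% is thus about 1 to 6 points with correlated shape, and about 11 to 13 points with independent, highly variable shape. It is larger if wounds barely shrink: with a control mean of 1.0 and ρ = 0.5, power is 77%, 73% and 66%.

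**5. Tracing is not error-free.** With an assumed 10% tracing error per visit (s = 0.08, ρ = 0.5, control mean 0.6), traced area has about 77% power against 78% for the product. The advantage is gone in that setting, although the calculation gives the product no reading error of its own.

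**The case against.** The strongest reply is that the text is loose rather than wrong. The data read in ImageJ could be two lengths or the area itself, and a condensed article may abbreviate a fuller instruction. This stands in part: the literal definition is the product, but confidence that a rectangle is what the reader will record can only be medium. If ImageJ area was intended, the item gives two different definitions and needs the same edit.

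Second, a reader might infer from the 27% figure that the treatment effect is biased by that amount. The documents do not support this. The factor is common to both arms and all visits, the Discussion interprets change in area, and no eligibility rule or threshold uses absolute area. Shape noise unrelated to treatment widens the comparison but does not tilt it.

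Third, the power figures depend wholly on assumed values, including the 80% starting point. One patient's ulcer shape is likely to be correlated over time, so the independent case is close to the worst on that input. A length-by-width index is simple and reproducible, and using one reader already limits variation. All of this stands, and it is why the point is minor.

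Fourth, wound area may not be the only healing information. The TCM syndrome score form is not shown and may contain wound items. The safe statement is that wound area is the only listed outcome that directly measures wound size.

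**Conclusion.** The point holds as a modest measurement improvement: minor severity, medium confidence. Read literally, section 3.2 fixes a cruder quantity than its own photographs and software allow. Absolute areas would be overstated by 27% for an ellipse on its own axes, and by more if the height is not taken perpendicular to the length. The group comparison is affected only through shape that varies between patients or visits.

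Under the main assumptions (relative-area SD 0.25, control mean 0.6, mean fill factor 0.75) the cost is about 1 to 6 power points with correlated shape and about 12 with independent, highly variable shape. It could be more if wounds hardly shrink, and nil if tracing error is about 10%. None of these inputs is in the document.

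A reader might also infer that the trial's size is called into question. It is not: section 2.4 sizes the trial on IL-6, so this point leaves the 60 patients and the primary outcomes untouched.

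**What to change.** In section 3.2, define wound area as the outline of the ulcer traced in ImageJ, in cm², calibrated to a scale placed in each photograph, and delete the length-by-height definition. If the product is kept, define length and perpendicular width and multiply by π/4. That corrects the average overstatement for oval wounds but not the error from changing shape.

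The cost is one line of text and a few minutes per image, with no extra visits, staff or patients. The downside is some manual tracing error, which keeping the same single reader helps to limit.

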### Safety assessment

3.3

Safety indicators will be reflected by blood cell analysis, urine routine, stool routine, liver function indicators, and kidney function indicators.

### Endpoint outcomes

3.4

Endpoint events refer to adverse cardiovascular and cerebrovascular events, including cardiovascular death, myocardial infarction, and ischemic stroke. In this study, the incidence and timing of endpoint events will be used as indicators for assessing endpoint outcomes. Researchers should keep detailed records of participants’ signs and symptoms. If the participant has any drug-related adverse events, the researchers will immediately submit it to the Ethics Review Committee of Hospital of Chengdu University of Traditional Chinese Medicine in the form of a written case report for identification.

### Statistical analysis

3.5

The data of the study will be analyzed by statistical analysis software packages SPSS 23.0 and will be performed by experts from the Statistics Teaching and Research Office of Chengdu University of Traditional Chinese Medicine. The measurement results was calculated by *t* test, and the results were expressed as “mean ± standard deviation.” Chi-squared test was used to analyze the count data. The paired design *t* test was used for comparison the differences between before and after treatment with the same group, and the independent sample *t* test was used for comparison the differences between groups. The comparison of incidence of adverse events between the 2 groups using Chi-squared test or Fisher exact probability method. If *P* < .05, it was considered as a statistically significant difference.

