### Design

2.1

This study is a multicenter, double-blind, randomized, placebo controlled clinical trial, and the protocol was registered in Chinese Clinical Trial Registry on July 16, 2019, ChiCTR1900024557. Sixty eligible participants signed the informed consent and were randomly assigned to the experimental or control group at a ratio of 1:2. Both groups received the same basic treatment for DF disease, the experimental group was additionally washed with FBD and ordinary dressing changes, while half of the patients in the control group received placebo and ordinary dressings, and the other half received placebo and silver ion dressings. The purpose of this trial is to explain the efficacy and safety of herbal medicine FBD for DFI compared with western medicine (WM) alone. This study will adhere to the standard protocol items: Recommendations for Interventional Trials (SPIRIT) 2013 statement, and flow chart of the study will be used to show the screening process (Fig. 1).

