### Treatment plan

3.1

Both groups received based on dietary treatments recommended by the Diabetes UK evidence-based nutrition guidelines for the prevention and management of diabetes,^[29]^ and controlled blood glucose, lowered blood lipids, adjusted blood pressure, and suppressed infections according to individual conditions during the trial period. At the same time, DF ulcers can be treated by surgical debridement to remove necrotic tissue, improve lower limb circulation and a routine dressing every 2 to 3 days according to the Diabetic Foot Ulcer Treatment Guidelines.^[30]^

Experimental group: The participants in experimental group took a foot bath 1 to 2 times a day. Each bag of FBD was dissolved in 300 mL of warm water for 30 minutes, then cover the wound with a ordinary dressing.

Control group: The patients in the control group will be given a placebo decoction for foot bath twice daily for 30 minutes. The immersion method is the same as the experimental group. In contrast, half of the patients covered the wound with an ordinary dressing and half with a silver ion dressing.

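### Continuous outcomes are tested only by unadjusted between-group and unranked within-group t tests, although baseline and weekly IL-6 and TNF-α are collected: valid, but inefficient and open to misreading

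*Protocol article*

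**What the plan says.** Section 3.5 (Statistical analysis) names two methods for measurement data. The paired-design *t* "test was used for comparison the differences between before and after treatment with the same group", and the independent-sample *t* "test was used for comparison the differences between groups". One significance level, P < .05, covers everything. The section does not rank the two tests, and it does not say whether the between-group test is applied to the endpoint value or to the change from baseline.

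Section 3.2 (Outcome measures) makes IL-6 and TNF-α primary; they "were measured before and each week after treatment during entire treatment". Section 2.1 has patients "randomly assigned to the experimental or control group at a ratio of 1:2", and section 2.4 turns this into 20 experimental and 40 control patients. Under section 3.1 the control group is itself divided: "half of the patients covered the wound with an ordinary dressing and half with a silver ion dressing". The same section gives every patient background care for glucose, lipids, blood pressure, infection and the ulcer.

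**The concern.** Two things are at stake.

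The first is precision. A t test on endpoint values makes no use of baseline. A t test on change uses it with a coefficient fixed at 1, which is rarely the best value. In a trial of 60 patients, which the Discussion itself calls small, a measured covariate that is left out of the analysis costs power that need not be lost.

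The second is interpretation. The trial's stated purpose is a comparison with western medicine alone. Since both groups receive active background care, improvement from baseline is plausible in both, and a before/after test within one group says nothing about the difference between them. With both kinds of test at P < .05 and neither declared decisive, the text leaves room to read significance in one group but not in the other as a treatment effect.

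**Working it through.** **Inputs from section 2.4.** "The mean values of the experimental group and the control group were 6.14 and 6.21", a difference of 0.07; "the combined standard deviation of the 2 groups was 0.14"; alpha 0.025 (taken as one-sided), beta 0.2; 20 and 40 patients. Not given, so assumed: the correlation r between baseline and follow-up (0.3 to 0.7), equal SDs at both times, and the standardised within-group change.

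**The plan's own figure.** The noncentrality of the two-sample t test is δ / (SD·√(1/n₁ + 1/n₂)). At 20/40 the denominator is 0.14 × √(0.05 + 0.025) = 0.0383. The article also says that "the optimal response rate was set to 0.04". If 0.04 is read as a margin (an assumption) and added to the difference, δ = 0.11, noncentrality is 2.87 and power 80.5%; this returns 20/40. With δ = 0.07 alone, noncentrality is 1.83 and power 43.5%, and 80% power would need 48/96 = 144. How the margin was used is a separate matter. I use 0.07 below because it is the stated difference in means.

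**Precision.** Variance relative to the endpoint t test is 1 for the endpoint test, 2(1 − r) for the change score and 1 − r² for ANCOVA. The ratio of ANCOVA to change score is (1 + r)/2. Power is from the noncentral t at 20/40, δ = 0.07, SD = 0.14 × √(relative variance), one-sided 0.025. The one degree of freedom spent on the covariate is ignored.

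| r | ANCOVA / endpoint variance | ANCOVA / change variance | Power, endpoint | Power, change | Power, ANCOVA |
|---|---|---|---|---|---|
| 0.3 | 0.91 | 0.65 | 43.5% | 32.9% | 46.9% |
| 0.5 | 0.75 | 0.75 | 43.5% | 43.5% | 54.5% |
| 0.7 | 0.51 | 0.85 | 43.5% | 64.0% | 71.0% |

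For 80% power at δ = 0.07 the total is 108 with ANCOVA against 144 with either t test at r = 0.5. At r = 0.7 it is 75, against 144 (endpoint) or 87 (change). The ordering does not depend on the choice of δ: at 0.11, ANCOVA gives 84.1%, 90.3% and 97.7%, against 80.5% (endpoint) or 66.4%, 80.5% and 95.4% (change).

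**Within-group tests.** Suppose both groups have the same true change of d SDs of change, so that there is no treatment difference. Let p₂₀ and p₄₀ be the power of the paired t test (two-sided 0.05, noncentrality d√n) in the two groups. Exactly one test is significant with probability p₂₀(1 − p₄₀) + p₄₀(1 − p₂₀). At d = 0.4: 0.397 × 0.306 + 0.694 × 0.603 = 0.121 + 0.418 = 0.540.

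| d | p₂₀ | p₄₀ | Control only | FBD only | Exactly one | Exactly one if 30/30 |
|---|---|---|---|---|---|---|
| 0.2 | 14% | 23% | 20% | 10% | 31% | 30% |
| 0.4 | 40% | 69% | 42% | 12% | 54% | 49% |
| 0.6 | 72% | 96% | 27% | 3% | 30% | 20% |
| 0.8 | 92% | 99.9% | 8% | 0.1% | 8% | 2% |

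The last column is 2p₃₀(1 − p₃₀). Unequal arms therefore add between about 0.5 and 10 percentage points. Where disagreement is most frequent, nearly all of it would occur with equal arms too. The 20/40 split mainly changes its direction: control alone comes out significant far more often than FBD alone.

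**The case against.** The independent-sample t test is a valid randomised comparison, and 20 against 40 does not bias it. Section 3.5 assigns the comparison of groups to that test, and section 2.4 sizes the trial on a two-sample comparison of means. All of this stands. A reader might infer that efficacy will be judged by setting the two within-group P values side by side, or that unequal arms create false contrasts in the planned analysis. The article supports neither: it nowhere states such a rule, and the table shows that equal arms would disagree nearly as often at 0.4 SD. If the two dressing halves of the control group were analysed separately, groups would be about 20 each and the size imbalance would vanish.

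A reader might also infer that the between-group test ignores baseline altogether. That holds only if it is run on endpoint values. If it is run on change, the gain from ANCOVA at r = 0.7 is from 64% to 71%, not from 43%.

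Finally, covariates, hospital effects, the week of analysis and a repeated-measures model are details that an article may leave to a fuller document. I therefore do not count their absence as an error. What remains open to criticism is the method the article does state: t tests only, with the within-group tests on the same footing as the between-group test.

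**Conclusion.** The point holds as one of efficiency and clarity, not of validity. Under either reading of the between-group test, ANCOVA is more precise across the assumed correlations: its variance is 0.91 to 0.51 of that of an endpoint t test, or 0.65 to 0.85 of that of a change-score t test. The power gain at δ = 0.07 runs from about 3 points (endpoint test, r = 0.3) to about 28 points (endpoint test, r = 0.7). Against a change score it is 7 to 14 points. The size rests on a correlation the article does not give, on equal SDs at both times, and on complete data.

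The within-group P values carry no information on the treatment difference. With no true difference they would disagree in 8% to 54% of trials over changes of 0.2 to 0.8 SD. This does harm only if they are read against each other, which the text permits but does not plan. Unequal arms are a secondary factor, and their tilt runs mostly against FBD. The matter should be corrected, but it does not invalidate the planned comparison.

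**What to change.** In section 3.5, name a baseline-adjusted between-group comparison as the deciding analysis for each continuous outcome: ANCOVA on the end-of-treatment value, with the baseline value as covariate. For IL-6 and TNF-α a mixed model over the weekly values, adjusted for baseline and with the treatment contrast at a named week, is an acceptable alternative. Report within-group change as mean and standard deviation or with a confidence interval, without P values. Hospital may be added as a covariate, but this is optional.

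The cost is a change of wording, made before the data are unblinded. The analyses are standard in the software already named, and no further data or visits are needed.
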